## Methods

### Study design

This is a double-center, double-blinded, randomized, controlled intervention trial. This study was registered under Chictr.org.cn (ChiCTR2200063844). This study will be conducted from 2022 to 2024 and reported in accordance with both the Consolidated Standards of Reporting Trials (CONSORT) statement and the CONSORT statement for non-pharmaceutical interventions [24, 25].

The primary objective of this trial is to investigate the facilitation (enhancement) effect of tDCS-induced neuroplasticity changes on the direct and migratory effects of WMT on cognitive function in schizophrenia. The secondary goals are to investigate the effects of tDCS and WMT on the brain plasticity and biological markers of patients with schizophrenia, and to examine the facilitation effect of tDCS on WMT-induced changes in brain plasticity and biological markers.

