### Sample size

The sample size was estimated based on the previous study reporting an effect size of 0.25 for observing the effect of CCRT on cognition [26]. With an alpha error estimate of 0.05 and power (1-β) of 0.90, 4 groups and 3 repeat measurements with a correlation among repetitive measures of 0.5 and nonsphericity correction of 1, a minimum sample size of 52 was required using G*Power 3.1.9.2 [27]. Accounting for the possibility of dropouts, the study adopts the block randomization to divide into groups with 8 patients in each block. The actual sample size of each group was 30 cases. Combining the clinical situations of each center, the Beijing and Chongqing centers were set to provide 80 and 40 patients, respectively.

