### Statistical analysis

Analyses will be performed according to the intent-to-treat (ITT) principle. Descriptive analysis will be performed on the data collected during each assessment at baseline, post-treatment, and the 3-month follow-up. The median and range describe continuous variables, and the frequencies and percentages describe qualitative variables.

Statistical significance will be set at *P* < 0.05, and corrected for multiple comparisons, when needed. To assess our primary endpoint criterion, that is, changes in cognitive performance, the outcomes at the three time points will be compared using a repeated-measures analysis of variance (ANOVA) with time (baseline, post-treatment, and 3-month follow-up) and group (tDCS + WMT, tDCS + SRT, sham tDCS + WMT, and sham tDCS + SRT) as factors. Further comparisons between the two groups can show the simple tDCS effect, simple WMT effect, and promoting effect of tDCS on WMT. Sensitivity analyses will be used to explore the effect of missing data due to loss to follow-up and dropout.

In cases where the data do not satisfy the assumption of normal distribution, the non-parametric Mann–Whitney *U* test will be used to compare the performance improvement between the four groups. SPM will be used to analyze imaging data to detect changes in brain function caused by cognitive training.

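### The fallback for non-normal data names a two-sample test for a four-group comparison, and it does not stand in for the group-by-time interaction the trial was sized on

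*Protocol article*

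**What the plan says.** All of the analysis wording is in the Statistical analysis section of the protocol article. The primary endpoint is to be analysed by "repeated-measures analysis of variance (ANOVA) with time (baseline, post-treatment, and 3-month follow-up) and group", with group having four levels. The section then adds: "Further comparisons between the two groups can show the simple tDCS effect, simple WMT effect, and promoting effect of tDCS on WMT". Significance is set at 0.05, with a general promise to correct for multiplicity where that is needed; no method is named.

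The fallback follows. Its trigger is worded as "In cases where the data do not satisfy the assumption of normal distribution". The method it then prescribes is that the "non-parametric Mann–Whitney *U* test will be used to compare the performance improvement between the four groups". It is not restricted to particular outcomes, so it can apply to the primary endpoint.

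Two other sections bear on it. Study design gives the primary objective as to "investigate the facilitation (enhancement) effect of tDCS-induced neuroplasticity changes on the direct and migratory effects of WMT". Sample size gives the inputs of the power calculation: "With an alpha error estimate of 0.05 and power (1-β) of 0.90, 4 groups and 3 repeat measurements", "an effect size of 0.25 for observing the effect of CCRT on cognition", and "a correlation among repetitive measures of 0.5 and nonsphericity correction of 1". These lead to a minimum of 52 patients, with 30 per group planned.

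**The concern.** Mann–Whitney is a two-sample rank test. The article assigns it a comparison across four arms, which it cannot make. This is a method stated wrongly rather than a detail left for later, so an analysis plan that followed the sentence would inherit the error.

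The fallback can also displace the primary analysis. The planned ANOVA gives one test of whether the four arms change differently over three visits. The fallback puts nothing equivalent in its place. An analyst would have to improvise, most naturally with pairwise tests of change. The article fixes neither the pairs nor the interval, and it does not say whether the multiplicity promise covers these tests.

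**Working it through.** **1. Which test was the trial sized on?** Inputs from Sample size: f = 0.25 (reading the stated effect size as Cohen's f, as G*Power uses for ANOVA), k = 4 groups, m = 3 measurements, ρ = 0.5, ε = 1, α = 0.05, power 0.90. For the within-between (group by time) interaction:

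λ = f²·N·m/(1 − ρ), df1 = (k − 1)(m − 1) = 6, df2 = (N − k)(m − 1)

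- N = 48: λ = 0.0625 × 48 × 3/0.5 = 18.0, df2 = 88, power 0.887
- N = 52: λ = 0.0625 × 52 × 3/0.5 = 19.5, df2 = 96, power 0.915

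With N rising in steps of 4, the first value to reach 0.90 is 52, which is the article's figure. The within-factor (time) test would need 36, and the between-factor (group) test would need 156. So the stated sample size rests on the 6-degree-of-freedom group-by-time interaction.

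**2. What can Mann–Whitney test here?** Applied to improvement scores, it compares the change of one pair of arms over one interval. That is a group-by-time question for that pair and interval. It is not the four-arm, three-visit interaction of step 1. Four arms give 4 × 3/2 = 6 pairs per outcome and interval.

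**3. What happens to the error rate if the tests are not corrected?** Treating tests as independent gives an upper guide: 1 − 0.95⁶ = 0.265 for six tests and 1 − 0.95³ = 0.143 for three. The tests share arms, so simulation is more realistic. With 4,000 null trials of four arms of 30 normal values, the share with at least one p < 0.05 was:

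| Procedure | At least one false positive |
|---|---|
| Six pairwise Mann–Whitney tests | about 19% |
| Three Mann–Whitney contrasts | about 12% |
| One Kruskal–Wallis test on four arms | about 5% |

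The article does not list the pairs behind its three effects. The 12% holds both for the study group against each other arm and for tDCS alone, WMT alone, and tDCS added to WMT.

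**4. Does a pairwise rank test address facilitation?** If facilitation means more than an additive effect, the contrast is (tDCS+WMT − sham+WMT) − (tDCS+SRT − sham+SRT). As an illustration, assume 0.5 SD for tDCS, 0.5 SD for WMT and no interaction; these values are not in the article. Mann–Whitney of tDCS+WMT against sham+WMT then rejects in about 45% of trials, and the difference-in-differences contrast in about 5%. The 45% depends on the assumed tDCS effect and falls to the nominal level if that effect is zero. The pairwise test is correctly detecting a tDCS effect among WMT patients; it does not show that the effect exceeds additivity.

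**The case against.** The best defence is that pairwise use was meant. The preceding paragraph speaks of two-group comparisons, and Mann–Whitney on improvement scores is a reasonable rank counterpart for simple effects. On that reading the sentence is loose rather than unsound. This softens the point but does not remove it: the sentence still says four groups, and no overall rank test is given.

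Four stronger conclusions are tempting, and the article does not support them.

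- **That the error rate is uncontrolled.** The same section promises correction where needed. The 19% and 12% describe what happens if it is not applied. Uncorrected parametric contrasts would raise the same multiplicity problem.
- **That the fallback tests nothing about group by time.** A between-arm comparison of change does test it, for one pair and one interval. What is lost is the joint interaction.
- **That the fallback is why facilitation goes untested, or why baseline and centre are not adjusted for.** The primary ANOVA has only time and a four-level group factor. It names no tDCS-by-WMT contrast, no baseline covariate and no centre term, so these gaps are not peculiar to the fallback.
- **That normality will be checked on raw values instead of residuals.** The wording is ordinary shorthand in a condensed article, and how the check is done is usual analysis-plan content.

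The fallback also applies only if normality fails. The article gives no distributional figures from which to judge how likely that is.

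**Conclusion.** Wrong as written; should be fixed. A two-sample test is named for a four-group comparison, and it can displace the group-by-time interaction from which the minimum of 52 was derived. That derivation assumes 0.25 is Cohen's f, and the match at 52 supports this reading.

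The error-rate figures are conditional: about 19% for six tests or 12% for three, for a single outcome and interval, under the global null, at 30 per arm with no dropout and no correction. The defect falls short of critical because it takes effect only when the normality condition fails, and the default analysis is untouched.

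**What to change.** Replace the fallback sentence. State that the planned group-by-time model and its named contrasts remain primary. If residuals are clearly non-normal, use bootstrap confidence intervals or a permutation test for those same contrasts, permuting according to the randomisation actually used. The article describes 15 blocks of 8 and does not mention stratification by centre, so the permutation scheme should not presume it.

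If a rank analysis is kept, label it a sensitivity analysis. Use Kruskal–Wallis on change scores across the four arms for a stated interval, followed by Mann–Whitney tests for pre-named pairs with Holm adjustment.

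The cost is a change of wording and a little more analysis work. No change to sample size or data collection is needed.

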## Discussion

As far as we know, working memory deficits are one of the core features of cognitive impairment and are closely related to social function in patients with schizophrenia. Although current WMT methods can improve cognitive performance, their overall and transfer effects are relatively low. More effective methods are urgently required to enhance the effects of WMT. This study is the first to combine tDCS stimulation with WMT to enhance the effect of WMT, altering the neuroplasticity of related brain regions in patients with schizophrenia.

This study has several strengths. As a well-documented effective method for altering brain plasticity, tDCS stimulation is used to modulate the functional state of brain regions prior to WMT, and functional MRI is used to explore the effects of tDCS on brain functional plasticity in patients with schizophrenia. In addition, a key issue for WMT mechanism studies is determining whether tDCS stimulation first activates local neuronal activity, subsequently enabling WMT to produce more pronounced changes in brain function. To determine this, we compare the tDCS + SRT and sham tDCS + WMT groups to explore whether the tDCS combined with the WMT approach would be superior to either in altering neuroplasticity (function and structure). Our findings help to confirm our hypothesis that tDCS can facilitate the clinical effect of WMT on cognitive improvement in schizophrenia and provide a scientific basis for exploring ways to enhance brain neuroplasticity and improve its function. Another strength of this trial is the exploration of the transfer effect, as our data will determine whether training, such as WMT, can improve untrained cognitive ability, including logical reasoning. The transfer effects of WMT on healthy individuals have already been confirmed, but few studies have investigated whether such effects also occur in schizophrenia. This study will fill this gap in knowledge.

This study has some limitations that must be addressed. First, the enrolled participants are not fully representative of a patient population with other comorbidities and considerable treatment heterogeneity. Therefore, we chose strict inclusion, exclusion, and dropping criteria to reduce the effects of confounding variables and to render the trial more accurate and realistic. Second, there may be challenges regarding the participants’ reaction to the trial, e.g., if the participant believes they are receiving sham treatment or if the treatment is too uncomfortable or too tiring. It is not clear whether participants will be able to distinguish between the real and sham treatments and the impact this may have on attrition rates.

## Trial status

This is the version of the protocol, dated September 19, 2022. Recruitment for this trial will begin soon and is expected to finish by the end of 2024.

## Data Availability

The datasets are available from the corresponding author upon request.

## Abbreviations

BDNF: Brain-derived neurotrophic factor
BNSS: Brief Negative Symptom Scale
BVMT: Brief Visuospatial Memory Test
CGI: Clinical Global Impression
CONSORT: Consolidated Standards of Reporting Trials
CPT: Continuous Performance Test
eCRF: Electronic case report form
FERT: Face Emotion Recognition Test
HVLT: Hopkins Verbal Learning and Memory Test
LTP: Long-term potentiation
LTD: Long-term depression
MCCB: MATRICS Consensus Cognitive Battery
MRI: Magnetic resonance imaging
PANSS: Positive and Negative Syndrome Scale
PSP: Personal and Social Performance Scale
SES: Self-Esteem Scale
SPIRIT: Standard Protocol Items Recommendations for Interventional Trials
SQOLS: Schizophrenia Quality of Life Scale
SRT: Simple response training
tDCS: Transcranial direct current stimulation
TEPS: Temporal Experience of Pleasure Scale
VERT: Vocal Emotion Recognition Test
WAIS-R: Wechsler Adult Intelligence Test Brief Version
WMT: Working memory training
